### Routine care

Participants in the control group will receive standard prenatal care and nutrition counseling according to guidelines of Ministry of Health of Chile. All pregnant women are weighed at each prenatal visit but any further advice is given regarding adequate weight gain.

### Outcomes

Primary outcomes will be: 1) for mothers: a) adequate weight gain at the end of the pregnancy based on IOM 2009 [30]; b) adequate glycaemic control at 24-28 weeks of pregnancy according to ADA 2011 (having fasting plasma glucose (FPG) levels <92 mg/dl or 2-h values in the oral glucose tolerance test (OGTT) of <153 mg/dl) [22]; 2) for infants: adequate weight, length and BMI growth during the first year of life according to WHO 2006 [31] (Table 2). Secondary outcomes will be divided into: i) implementation outcomes (number of midwives and dietitians per PHCC, compliance to protocol by health personnel, time allocated to the actions of the interventions, etc.) and ii) participant compliance outcomes (attendance to dietitian's clinic, attendance to PA sessions, etc.).

**Table 2 Tab2:** Outcomes of the intervention

Goal	Indicator
Healthy weight gain during Pregnancy^a^	Based on pre-conceptional nutritional status:
	Normal (BMI 18.5-24.9 kg/m^2^) =11.5-16.0 kg
	Overweight (BMI 25.0-29.9 kg/m^2^) = 7.0-11.5 kg
	Obese (BMI ≥30 kg/m^2^) = 5.0-9.0 kg
Adequate Glycaemic control during Pregnancy^b^	Fasting plasma glucose (FPG) levels <92 mg/dl or 2-h values in the 75-g oral glucose tolerance test (OGTT) of <153 mg/dl at 24-28 weeks of pregnancy
Healthy infant growth^c^from 0-1 y	Weight-for-age, height-for-age and BMI-for-age Z-scores based on WHO standards (between -2 and +2SD)

^a^Institute of Medicine (US) and National Research Council, Weight Gain During Pregnancy: Reexamining the Guidelines, 2009

^b^Diabetes Care, Vol. 34, Supplement 1, January 2011

^c^The Who Child Growth Standards, 2006

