### Sample size

The sample size was estimated based on the hypothesized effect sizes using existing data, and the likely rates of study drop-out (20 %). Assuming that currently 50 % of Chilean women meet Institute of Medicine (IOM) weight gain recommendations [32], that we have six intervened and six control health centers, two-tail α p < 0.05; 80 % power and an intraclass correlation coefficient of 0.008 % [33] (based on cluster design of the study), we will need to recruit 200 women in each PHCC (n = 1200 per arm to obtain a final sample size of 960 per arm) to detect a 20 % difference in the achievement of IOM weight gain recommendations between intervened and control women.

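### The glycaemic primary outcome joins its two thresholds with 'or', so as written a woman with one glucose value above the protocol's own limit counts as adequately controlled

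*Protocol article*

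**What the plan says.** The Outcomes section of the protocol article lists, as the second primary outcome for mothers, "adequate glycaemic control at 24-28 weeks of pregnancy according to ADA 2011", and spells it out in brackets as "having fasting plasma glucose (FPG) levels <92 mg/dl or 2-h values in the oral glucose tolerance test (OGTT) of <153 mg/dl". Table 2, which sets an indicator against each goal, gives the same rule: "Fasting plasma glucose (FPG) levels <92 mg/dl or 2-h values in the 75-g oral glucose tolerance test (OGTT) of <153 mg/dl". Both places use 'or'. The Abstract names the outcome without thresholds. No section says that both values must be below their limits, and none says that 'or' means whichever test happens to be on record.

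The Sample size section deals with weight gain only. It starts from "Assuming that currently 50 % of Chilean women meet Institute of Medicine (IOM) weight gain recommendations" and sizes the trial "to detect a 20 % difference in the achievement of IOM weight gain recommendations". It gives no expected rate for the glycaemic outcome.

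**The concern.** The outcome is labelled adequate control, and the protocol sets two limits for it. Under 'or', breaching one limit does not matter as long as the other is met. A woman with FPG 85 and a 2-h value of 180 mg/dl, or with FPG 100 and a 2-h value of 140 mg/dl, would be a success on a primary outcome. A likely origin is a rule for abnormality (either value raised) that was turned into a rule for normality without changing 'or' to 'and'.

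At stake is the meaning of one primary result. A proportion reported as adequately controlled would include every woman with exactly one raised value, and the comparison between arms would rest on the smaller group with both values raised.

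**Working it through.** **Step 1. The rule as logic.** Inputs: the two thresholds in the Outcomes text and Table 2.

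| FPG <92 | 2-h <153 | 'or' (as written) | 'and' |
|---|---|---|---|
| yes | yes | adequate | adequate |
| yes | no | adequate | not adequate |
| no | yes | adequate | not adequate |
| no | no | not adequate | not adequate |

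The rules differ only in the two middle rows, always in the same direction. With A = raised FPG and B = raised 2-h value:

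- failures under 'or' = P(A and B)
- failures under 'and' = P(A) + P(B) − P(A and B)
- difference = P(exactly one raised) ≥ 0

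This needs no assumption about the glucose distribution.

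**Step 2. Illustrative size.** The article has no figure to reproduce, so every input here is assumed: bivariate normal values, FPG mean 82 and SD 9, 2-h mean 115 and SD 28 mg/dl, correlation 0.5.

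- P(A) = P(Z ≥ (92 − 82)/9) = 0.133
- P(B) = P(Z ≥ (153 − 115)/28) = 0.087
- P(A and B) = 0.036 (bivariate normal upper tail)
- P(A or B) = 0.133 + 0.087 − 0.036 = 0.185 (from unrounded values)
- exactly one raised = 0.185 − 0.036 = 0.149
- share of women with a raised value who are scored adequate = 0.149 / 0.185, about 81%

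The planned sample is "n = 1200 per arm to obtain a final sample size of 960 per arm". If all 960 had both results, that is about 34 failures per arm under 'or' and about 177 under 'and'.

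**Step 3. Range over assumptions.**

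| Assumed raised rates | Correlation | Failures, 'or' | Failures, 'and' |
|---|---|---|---|
| 5-15% for each test | 0 to 0.7 | 0.3-7.8% | 8.0-27.8% |
| FPG 7-22%, 2-h 4-12% | 0.3 to 0.6 | 1-7% | 9-29% |
| 10% for each test | 0.9 | 6.9% | 13.1% |

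Even in the last row, (13.1 − 6.9)/13.1, about 47% of women with a raised value, are scored adequate.

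**Step 4. Women with one result only.** Under 'and', a single raised value already settles failure, while a single normal value leaves the outcome unknown. It is natural to set only the latter to missing, but that keeps one-test women in the analysis only when they fail. Using the Step 2 inputs, suppose a fraction s of women, chosen without regard to glucose, have FPG only:

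observed failure rate = [(1 − s) × 0.185 + s × 0.133] / [(1 − s) + s × 0.133]

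- s = 0.3: 0.169 / 0.740 = 22.9%
- s = 0.5: 0.159 / 0.567 = 28.1%

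The true rate is 18.5%. Treating every one-test woman as incomplete returns 18.5% in both cases, provided that the missing test is unrelated to glucose.

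**The case against.** The strongest reply is that the bracket is shorthand. The outcome is tied to a cited standard, and the bracket may only list that standard's cut-offs, or may mean whichever of the two tests was recorded, since the Data collection section draws on routine records. This stands in part: the wording does not prove that the trial will code a woman with one raised value as a success. It does not rescue the text. Neither reading is stated, and the 'whichever test' reading leaves a woman with both results, one of them raised, without a class. The argument here rests on the protocol's own label and limits, not on the content of the cited standard.

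Three stronger inferences are tempting, and the documents do not support them:

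- **Most women with hyperglycaemia become successes and the success rate nears 100%.** That depends on rates and a correlation that the article does not give.
- **A real effect would be missed.** No effect size or event rate is stated for this outcome, so no power statement can be made in either direction.
- **OGTT uptake will differ by arm and bias the result.** Nothing in the article suggests this. The Intervention section and Table 1 contain no glucose-testing component.

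It is also fair to say that weight gain, on which the sample size rests, and infant growth are untouched.

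**Conclusion.** The definition is wrong as written, in both places where it appears, and it governs a primary outcome. Two things hold without assumptions: a woman who breaches one of the protocol's two limits is scored as adequate, and 'or' gives fewer failures than 'and' whenever any woman has exactly one raised value. The size is illustrative only. Under the assumed bivariate normal model, failures of 18.5% fall to 3.6%, and the ranges in the working show how far this moves with other inputs. The conclusion is confined to what the reported proportion means; it does not extend to power or to bias between arms.

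**What to change.** In the Outcomes text and in Table 2, define adequate glycaemic control as FPG <92 mg/dl **and** 2-h OGTT <153 mg/dl at 24-28 weeks. This changes how the endpoint is coded, not how any woman is treated.

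State in advance how women with only one of the two results are handled, with the same rule whether that result is normal or raised. One option is to treat the outcome as incomplete for all of them and add a sensitivity analysis. Do not set it to missing only when the single value is normal.

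The cost is one word in two places and a coding rule. The success proportion will look less favourable, and treating all one-test women as incomplete sets aside some known failures, which the sensitivity analysis can bring back.

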### Data collection

All data will be collected as part of routine health care activities. Study PHCCs have implemented electronic health records since 2009. Contact, sociodemographic information (eg. age, marital status, schooling, family structure, parity, etc.) and pre-pregnancy weight will be obtained from health records and by direct questioning at recruitment. All data related to pregnancy, delivery and offspring´s health are registered in a standardized manner in electronic health records; this system will allow evaluating all study outcomes. Electronic records will also provide with implementation and compliance data, which will be complemented with data obtained by the study coordinator by phone calls to a random sample of professionals and participants each two months. PA instructors will record PA attendance by participants at each session.

### Sample size

The sample size was estimated based on the hypothesized effect sizes using existing data, and the likely rates of study drop-out (20 %). Assuming that currently 50 % of Chilean women meet Institute of Medicine (IOM) weight gain recommendations [32], that we have six intervened and six control health centers, two-tail α p < 0.05; 80 % power and an intraclass correlation coefficient of 0.008 % [33] (based on cluster design of the study), we will need to recruit 200 women in each PHCC (n = 1200 per arm to obtain a final sample size of 960 per arm) to detect a 20 % difference in the achievement of IOM weight gain recommendations between intervened and control women.

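### The sample size of 960 per arm does not follow from its printed inputs: an ICC of 0.008 % and a 20 % difference need about 91 to 94 women per arm, or about 390 if the difference is relative

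*Protocol article*

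**What the plan says.** The Sample size section of the protocol article gives a full set of inputs and a result:

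- Control proportion: "Assuming that currently 50 % of Chilean women meet Institute of Medicine (IOM) weight gain recommendations".
- Clusters: "that we have six intervened and six control health centers".
- Error rates: "two-tail α p < 0.05", with 80 % power.
- Clustering: "an intraclass correlation coefficient of 0.008 % [33] (based on cluster design of the study").
- Result: 200 women recruited per centre, "n = 1200 per arm to obtain a final sample size of 960 per arm", after 20 % drop-out.
- Target: "to detect a 20 % difference in the achievement of IOM weight gain recommendations between intervened and control women".

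The paragraph does not say whether the 20 % is absolute or relative. It gives no design effect and no second proportion. The Statistical methods section says that all analyses will allow for clustering through multi-level regression.

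**The concern.** An ICC of 0.008 % is effectively zero. If it were right, clustering would cost nothing, and a 20-point difference from 50 % would need roughly a tenth of the women planned. The paragraph asks for 960 per arm, so the ICC, the target difference or both are not as printed.

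This is the only sample size justification in the article, and it concerns a primary outcome. A target of 10 points rather than 20 changes how a null result is read. Anyone who reused the printed ICC to plan another trial in these centres would ignore clustering.

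**Working it through.** **Inputs** (all from the Sample size section): p1 = 0.50; p2 = 0.70 if the 20 % is absolute, 0.60 if relative; two-sided α = 0.05 (z = 1.96); 80 % power (z = 0.8416); k = 6 centres per arm; m = 960/6 = 160 analysed per centre; ICC = 0.00008 as printed, or 0.008 if the percent sign is a slip.

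**Drop-out step.** 960/0.8 = 1200 per arm, and 1200/6 = 200 per centre. This part is correct.

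**Individually randomised size.** n = (1.96 + 0.8416)² × [p1(1−p1) + p2(1−p2)]/d², with (1.96 + 0.8416)² = 7.849.

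- 50 v 70 %: 7.849 × 0.46/0.04 = 90 (93 with pooled variance).
- 50 v 60 %: 7.849 × 0.49/0.01 = 385 (387 with pooled variance).

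**Design effect.** DE = 1 + (m − 1) × ICC.

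- ICC 0.00008: 1 + 159 × 0.00008 = 1.013.
- ICC 0.008: 1 + 159 × 0.008 = 2.272.

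**Needed per arm, and power at 960 per arm:**

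| ICC | Proportions | Needed per arm | Power, normal | Power, t on 10 df |
|---|---|---|---|---|
| 0.00008 (as printed) | 50 v 70 % | 91–94 | >99.9 % | >99.9 % |
| 0.00008 (as printed) | 50 v 60 % | 389–392 | 99 % | 98 % |
| 0.008 | 50 v 70 % | 205–211 | >99.9 % | >99.9 % |
| 0.008 | 50 v 60 % | 874–880 | 83.6 % | 75.4 % |

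The stated 960 is not reproduced in any row. Continuity correction does not rescue the literal reading (105 per arm for 50 v 70 %), and neither does a 10-df reference (about 114). An ICC of 0.08 with 50 v 70 % overshoots, at about 1238 to 1276.

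**The nearest reading in detail (ICC 0.008, 50 v 60 %).**

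- The 874 to 880 holds the design effect at m = 160. With six centres per arm fixed, m solves 6m = n[1 + (m − 1) × ICC], so m = n(1 − ICC)/(6 − n × ICC). For n = 385 to 387 this is about 131 to 132 per centre, or 783 to 795 per arm. With continuity correction and m = 160 the figure is 927.
- Power at 960: SE = √(0.49 × 2.272/960) = 0.0341, and 0.10/0.0341 = 2.94. The normal reference gives 83.6 %. A noncentral t on 2 × 6 − 2 = 10 df gives 75.4 %, and a simulated cluster-level t-test gave 75.1 %.
- Detectable difference at 80 % power: about 9.5 points on the normal reference, 10.6 points on 10 df.

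**The case against.** The best defence is that the percent sign is a slip and the 20 % is relative. The stated 80 % is then met on the usual normal design-effect calculation (83.6 %), and a round 200 per centre is simply more than the minimum. That is plausible, and under it the planned number is not an arithmetic error. But it needs two departures from a plain reading of the text, and the ICC's source is not at hand. It explains the figure without making the paragraph correct as written.

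A reader might go further and infer that the trial falls short of its 80 % power. The document does not support that. The 75 % appears only with a 10-df t reference. Such a reference suits a comparison of 12 centres, but the article names no reference distribution, and that choice is commonly left to an analysis plan. If the printed ICC were right, there would be no shortfall at all.

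Nor does it follow that more women must be recruited. On 10 df, holding 80 % power for 50 v 60 % at ICC 0.008 would take about 213 analysed women per centre (1278 per arm). Restating the power or the detectable difference is an equally honest course, and the choice is the sponsor's.

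**Conclusion.** The statement is wrong as written. The printed inputs call for 91 to 94 women per arm (389 to 392 if the 20 % is relative), against 960 stated. This rests on nothing beyond standard formulas, and no choice among them closes the gap.

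That an ICC of 0.008 and a 10-point difference were intended is an inference, drawn because it is the only reading examined that comes near 960. If it is confirmed, power is about 84 % by normal approximation and about 75 % on 10 df. The second figure is conditional on that reference and does not show that the design is underpowered.

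**What to change.** Rewrite the paragraph:

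1. Check the ICC against the cited source and state it as a proportion.
2. State both target proportions, and whether the 20 % is absolute or relative.
3. Give the design effect and the analysed cluster size it uses (2.27 at 160 per centre, if the ICC is 0.008).
4. If ICC 0.008 and 50 v 60 % are confirmed, state power with its reference distribution: about 84 % by normal approximation and about 75 % on 10 df, or a detectable difference of 10.6 points at 80 % power on 10 df. If the source gives other values, recompute.

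The cost is one reworded paragraph. Enrolment need not change. The downside is a less favourable stated power on the small-sample reference.

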### Statistical methods

Data analyses will be conducted by statisticians who will be blinded to the treatment allocation. Primary analyses will be carried out based on the allocation to each study group (“intention to treat”). Results will be presented as appropriate effect sizes with a measure of precision (95 % confidence intervals). All analyses will take into account the clustered design of the study (i.e. conduct multi-level regression analyses –hierarchical and longitudinal). Adjustment in the analyses will be done if there is baseline imbalance in covariates. Further exploratory analyses will be based on those participants who fully follow the protocol (“per-protocol analyses”).

### Safety monitoring

We will establish a data safety monitoring board with nutrition, obstetric, endocrinologist, and statistics experts. This group will be responsible for reviewing clinical trial data on an ongoing basis to ensure the safety of study subjects, as well as validity and integrity of the data**.**

### Ethical approval

The protocol for this study has been approved by the Institute of Nutrition and Food Technology of University of Chile, the Catholic University of Chile, and the South-Eastern Health Service Ethics committees. Potential participants will be provided with detailed information by the project field staff on the nature and relevance of the trial and the actions involved if they agree to participate. Potential participants will then be asked to sign a written consent form.

## Discussion

We expect that the intervention will benefit the participants in achieving adequate weight gain & metabolic control during pregnancy as well as adequate infant growth as a result of an increased impact of standard nutrition and health care practices. The results should be potentially extended to the rest of the primary health care system given the project´s "program effectiveness" approach and the participation of the Ministry of Health in the study design. Gathered information should contribute to a better understanding of how to develop effective interventions to halt the maternal obesity epidemic and its associated co-morbidities in the Chilean population.

## Abbreviations

NCDs: Non-communicable chronic diseases
PA: Physical activity
CHiMINCs: Chilean maternal and infant nutrition cohort study
PHCCs: Public health care centers
BMI: Body mass index
BF: Breastfeeding
